### **14.2 Adverse events**

Adverse events (AEs) are defined as any untoward medical occurrence in a patient or clinical investigation participant administered an investigational intervention and which does not necessarily have to have a causal relationship with this treatment (adapted from the Note for Guidance on Clinical Safety Data Management: Definitions and Standards for Expedited Reporting (CPMP/ICH/377/95 July 2000)).

It is recognised, however, that the participant population with severe sepsis in the ED and ICU will experience a number of common aberrations in laboratory values, signs and symptoms due to the severity of the underlying disease and the impact of standard therapies. These will not necessarily constitute an adverse event unless they require significant intervention and are deemed to be causally related to the study intervention arms (possibly, probably or definitely) by the investigator or are considered to be of concern in the investigator's clinical judgement. Adverse events already defined as study complication outcomes (e.g. CVC complications, acute pulmonary oedema, vasopressor complications) will not be reported separately as adverse events to facilitate unbiased reporting. In all cases, the condition or disease underlying the symptom, sign or laboratory value should be reported e.g. pulmonary oedema rather than bilateral inspiratory auscultatory crackles.

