## 1. ABBREVIATIONS

|              |                                                                                                       |
|--------------|-------------------------------------------------------------------------------------------------------|
| ACEM CTN     | Australasian College for Emergency Medicine Clinical Trials Network                                   |
| AE           | Adverse event                                                                                         |
| ANP          | Atrial Natriuretic Peptide                                                                            |
| ANZIC-RC     | Australian and New Zealand Intensive Care Research Centre                                             |
| ANZICS CTG   | Australian and New Zealand Intensive Care Society Clinical Trials Group                               |
| APACHE II    | Acute Physiologic Assessment and Chronic Health Evaluation II                                         |
| APO          | Acute pulmonary oedema                                                                                |
| ARISE FLUIDS | Australasian Resuscitation In Sepsis Evaluation: FLUId or vasopressors In emergency Department Sepsis |
| ARISE        | Australasian Resuscitation In Sepsis Evaluation                                                       |
| CI           | Confidence interval                                                                                   |
| CLASSIC      | Conservative versus Liberal Approach to Fluid Therapy of Septic Shock in Intensive Care               |
| CLOVERS      | Crystalloid Liberal versus Vasopressors Early                                                         |
| CVC          | Central venous catheter                                                                               |
| DAOH-D90     | Days alive and out of hospital to day 90                                                              |
| DSMC         | Data Safety Monitoring Committee                                                                      |
| E/CRF        | Electronic/case report form                                                                           |
| ED           | Emergency department                                                                                  |
| EG           | Endothelial glycocalyx                                                                                |

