### 8.2 Secondary outcomes

1. All-cause mortality at 90 days
2. Time from randomisation until death (to day 90)
3. Days alive and at home at 90 days post-randomisation
4. Ventilator-free days to day 28
5. Vasopressor-free days to day 28
6. Renal replacement therapy-free days to day 28
7. Death or disability at 6 and 12 months\*

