### 8.3 Tertiary outcomes

1. Incidence and duration of invasive mechanical ventilation
2. Incidence and duration of vasopressor support
3. Incidence and duration of acute renal replacement therapy
4. ED length of stay
5. ICU length of stay
6. Hospital length of stay
7. In hospital mortality (censored at 90 days)

8. Mortality at 6 and 12 months\*
9. Quality of life at 6 and 12 months\*
10. Cost-effectiveness measured as cost/QALY\*

\*May be reported separately when 12-month follow up complete

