### **4. Other data**

- Daily fluid balance until day 7 post-randomisation or ICU discharge whichever occurs first
- Source of infection and microbial culture results
- Type and timing of IV antimicrobials
- Type and timing of co-interventions e.g. source control procedure, corticosteroids, extracorporeal membrane oxygenation
- CVC insertion date and time
- Complication outcomes (CVC complications, APO, ischaemic events)
- Date and time consent granted or the date the study brochure presented
- Treatment limitations or withdrawal
- Patient clinical costings for index admission

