### 14.3 Serious adverse events

The baseline mortality of participant with septic shock is high. Such patients will frequently develop life-threatening organ failure(s) unrelated to the study interventions and despite optimal management. Therefore, events that are part of the natural history of the disease process or are expected complications of septic shock will not be reported as serious adverse events in this study. In particular, events already defined as study outcomes (e.g. death, readmission) will not be reported separately as serious adverse events unless they are considered to be causally related to the study intervention or are otherwise a concern in the investigator's judgement.

SAEs will be defined in accordance with the Note for Guidance on Clinical Safety Data Management: Definitions and Standards for Expedited Reporting (CPMP/ICH/377/95) (July 2000) as any untoward medical occurrence that:

- Results in death
- Is life-threatening
- Requires inpatient hospitalisation or prolongation of existing hospitalisation
- Results in persistent or significant disability/incapacity
- Is a congenital anomaly/birth defect
- Is an important medical event which may require intervention to prevent one of the previously listed outcomes

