### 14.4 Reporting

AEs and SAEs, which are deemed causally related to the study intervention by the investigator, will be collected from randomisation up to hospital discharge.

SAEs will be reported to the coordination centre within 24 hours of the site investigator becoming aware via completion of the SAE form on the website. Minimum data will include the patient study ID, nature of the event, commencement and cessation of the event, the investigators opinion of the relationship of the event to the trial

(possibly, probably or definitely related), and any treatment which was required. The investigator should notify the Institutional/Ethics Committee of the occurrence of the serious adverse event or any significant safety issues in accordance with local jurisdictional requirements/policy directives.

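### Vasopressor complications are excluded from adverse-event reporting as already-defined complication outcomes, but they are missing from the complication list in 12.2 and from the outcomes in section 8

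*Protocol*

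**What the plan says.** Section 14.2 takes a group of events out of adverse-event reporting: "Adverse events already defined as study complication outcomes (e.g. CVC complications, acute pulmonary oedema, vasopressor complications) will not be reported separately as adverse events". The reason given at the end of that sentence is to keep reporting unbiased.

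The only other place where the protocol uses the idea of a complication outcome is the data list in section 12.2, item 4: "Complication outcomes (CVC complications, APO, ischaemic events". The abbreviations list expands APO as "Acute pulmonary oedema", so that entry is the same event as in 14.2.

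Section 8 and the synopsis give one primary, seven secondary and ten tertiary outcomes. They cover survival, days out of hospital, organ support, length of stay, function, quality of life and cost. Typical entries are "Renal replacement therapy-free days to day 28" and "Incidence and duration of acute renal replacement therapy". No complication is among them.

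For adverse events that remain reportable, section 14.4 sets the scope: "AEs and SAEs, which are deemed causally related to the study intervention by the investigator, will be collected from randomisation up to hospital discharge". Section 14.3 lets events that are study outcomes still be reported as serious adverse events if judged related or worrying. Section 10.6 allows vasopressors through a peripheral line for up to 24 hours.

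**The concern.** An event may reasonably be kept out of adverse-event reports when it is recorded systematically as an outcome. That gives cleaner data than reports from unblinded investigators. The arrangement works only if the list of excluded events and the list of recorded events are the same. Here they are not: 14.2 names vasopressor complications where 12.2 names ischaemic events, and section 8 names neither.

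What is at stake is one class of local harm from the drug infusion. Section 6 says that starting vasopressors peripherally is meant to bring them in sooner, and early introduction is what defines one of the two arms. A safety comparison that leaves out infusion-site injury could therefore miss a harm of the strategy that the trial hypothesises to be better. The protocol also rests enrolment without prior consent (11.5.3) on the position that taking part adds no clinical risk over routine care. That makes full capture of strategy-specific harm more important.

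**Working it through.** The protocol gives no figure to reproduce, so the check compares the sections category by category.

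| Category | Excluded from AE reports (14.2) | Named data item (12.2) | Listed outcome (section 8, synopsis) |
|---|---|---|---|
| CVC complications | yes | yes | no |
| Acute pulmonary oedema | yes | yes, as APO | no |
| Vasopressor complications | yes | no; ischaemic events overlap in part | no |
| Ischaemic events | not named | yes | no |

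1. **Outcome lists.** 1 + 7 + 10 = 18 outcomes, of which 0 are complications. All three excluded categories (3 of 3) are absent from section 8.
2. **Data collection.** Two of the three excluded categories are named in 12.2. The third is covered only where the complication is ischaemic.
3. **Who is covered.** Section 12.1 asks for complete data on everyone randomised, and 12.2 attaches no causality condition to the complication items. CVC complications, pulmonary oedema and ischaemic events are therefore planned for both arms.
4. **What is left.** Take a vasopressor complication that is neither ischaemic nor serious, such as a local injury at a peripheral infusion site. Section 14.2 bars it from adverse-event reporting. Section 12.2 has no item for it. The exception in 14.3, "unless they are considered to be causally related to the study intervention or are otherwise a concern", applies to serious events, and 14.2 has no counterpart for non-serious ones. No stated route remains.
5. **Direction.** Section 10.3 stops fluid resuscitation and starts a vasopressor if hypotension or hypoperfusion persists. Section 10.4 brings vasopressors in later. More early peripheral infusion in the first arm is the natural expectation, but the protocol gives no rate. The pilot trial described in section 6 found similar rates of vasopressor use in its two arms, and median durations of 20 hours (restricted) and 33 hours (standard). A larger total exposure in the early arm is therefore not established.

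Two related slips came up in the check. The sentence that follows the exclusion in 14.2 uses pulmonary oedema as its example of a condition to report, just after acute pulmonary oedema has been excluded. Section 12.2, item 5, sends the reader to section 13 for adverse events, which are in section 14.

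**The case against.** The strongest reply is that most of these harms are well provided for. Section 12.2 lists complication outcomes under nearly the name that 14.2 uses, and 12.1 extends collection to every participant. Recording pulmonary oedema, line complications and ischaemia as outcomes keeps them out of the open-label causality judgement in 14.4. That is better than reporting them as adverse events. This stands in full.

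A reader might infer from section 8 alone that the key harms drop out of the comparison, or that planned capture of vasopressor complications is zero. The documents support neither reading. Three kinds of complication are planned data items in both arms. Ischaemic events take in part of vasopressor harm, since 10.5.2 speaks of both bowel and limb or digit ischaemia. A serious event judged related can still be reported under 14.3. The DSMC receives all serious-event reports and may ask for any other data (14.1). How complications are analysed and tabulated may properly be left to the statistical analysis plan, which is not shown. Limiting the remaining adverse events to those judged related is a design choice that the protocol explains, and it is not faulted here.

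It can also be said that the list in 12.2 is introduced as inclusive, that the synopsis introduces its tertiary outcomes in the same way, and that the CRF is not shown and may hold a suitable field. That is possible. A site might also reason that an event missing from 12.2 is not yet defined as an outcome and so stays reportable. But 14.2 names vasopressor complications expressly, and even on that reading 14.4 would admit only events judged related to the intervention. The mismatch therefore still needs correcting. An analysis plan cannot recover events that sites were told not to report and had no field to record.

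**Conclusion.** The point holds as an inconsistency between 14.2, 12.2 and section 8, with one practical consequence. Non-serious, non-ischaemic vasopressor complications are excluded from adverse-event reporting and have no named data item. In size, that is one of three excluded categories at best partly collected, with all three absent from the listed outcomes. The number of events that could be missed cannot be estimated from the protocol.

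The conclusion assumes that the data items in 12.2 reflect what the CRF asks for and that sites follow 14.2 as written. That the harm falls more on the early-vasopressor arm is likely from the design, but it is an inference. The point should be fixed because the remedy is specific and cheap and because data not recorded prospectively may be hard to recover. It does not threaten the primary comparison or the planned capture of pulmonary oedema, line complications or ischaemia.

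**What to change.** - Make the complication lists in 12.2 and 14.2 identical: CVC complications, vasopressor or infusion-site complications, acute pulmonary oedema and ischaemic events.
- Define each item and record it for every participant over one fixed window from randomisation, whatever the judged causality.
- Add these complications to 8.3 and the synopsis, so that a comparison by arm is planned.
- Reconcile the sentence in 14.2 that gives pulmonary oedema as an example of something to report with the exclusion just before it.
- Correct the cross-reference in 12.2, item 5, to section 14.

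The cost is a protocol wording change, one or two CRF fields and a little extra data entry. No change to treatment, sample size or the primary analysis is involved.

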### 14.3 Serious adverse events

The baseline mortality of participant with septic shock is high. Such patients will frequently develop life-threatening organ failure(s) unrelated to the study interventions and despite optimal management. Therefore, events that are part of the natural history of the disease process or are expected complications of septic shock will not be reported as serious adverse events in this study. In particular, events already defined as study outcomes (e.g. death, readmission) will not be reported separately as serious adverse events unless they are considered to be causally related to the study intervention or are otherwise a concern in the investigator's judgement.

SAEs will be defined in accordance with the Note for Guidance on Clinical Safety Data Management: Definitions and Standards for Expedited Reporting (CPMP/ICH/377/95) (July 2000) as any untoward medical occurrence that:

- Results in death
- Is life-threatening
- Requires inpatient hospitalisation or prolongation of existing hospitalisation
- Results in persistent or significant disability/incapacity
- Is a congenital anomaly/birth defect
- Is an important medical event which may require intervention to prevent one of the previously listed outcomes

### 14.4 Reporting

AEs and SAEs, which are deemed causally related to the study intervention by the investigator, will be collected from randomisation up to hospital discharge.

SAEs will be reported to the coordination centre within 24 hours of the site investigator becoming aware via completion of the SAE form on the website. Minimum data will include the patient study ID, nature of the event, commencement and cessation of the event, the investigators opinion of the relationship of the event to the trial

(possibly, probably or definitely related), and any treatment which was required. The investigator should notify the Institutional/Ethics Committee of the occurrence of the serious adverse event or any significant safety issues in accordance with local jurisdictional requirements/policy directives.

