### **10.10 Bias Minimisation**

Given the nature of the intervention, it is impossible to blind treating clinicians and participants for logistical and safety reasons. Study treatment assignment will be revealed to treating staff as they are required to apply their clinical judgement in the delivery of the trial protocol.

Bias will be minimised by:

1. ensuring concealment of the treatment allocation until completion of the randomisation procedure
2. regular monitoring and reporting of protocol compliance and

3. an objective primary outcome measure which is not susceptible to ascertainment bias.

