## **14. SAFETY**

### **14.1 Data Safety Monitoring Committee**

An independent data safety monitoring committee (DSMC), comprising experts in clinical trials, biostatistics, emergency medicine and intensive care has been established before participant enrolment and will review all trial protocols. The committee will be charged with monitoring trial safety and efficacy and overseeing the interim analysis. The DSMC may, in its absolute discretion, request assessment of any other trial data at any time.

The project manager will forward a copy of all serious adverse event (SAE) reports as soon as they become available to the DSMC or at the discretion of the DSMC, their delegated independent safety monitor. The DSMC or their delegated independent safety monitor will review all SAE reports that are received and the DSMC may report back to the management committee of the study if any further action is required.

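### Section 14.4 collects only events judged causally related, although Sections 14.2 and 14.3 also make some events reportable because they concern the investigator

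*Protocol*

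**What the plan says.** Section 14.2 starts from a definition of an adverse event that does not require a causal link. It then sets aside the abnormal laboratory results, signs and symptoms that are usual in this illness, with two ways back in. They need not be adverse events "unless they require significant intervention and are deemed to be causally related to the study intervention arms (possibly, probably or definitely) by the investigator", and the sentence then adds "or are considered to be of concern in the investigator's clinical judgement".

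Section 14.3 exempts natural-history events and expected complications from SAE reporting. For events already defined as study outcomes, with death and readmission as its examples, it lifts the exemption if they are thought causally related "or are otherwise a concern in the" investigator's judgement.

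Section 14.4 states what is collected, from randomisation to hospital discharge: "AEs and SAEs, which are deemed causally related to the study intervention by the investigator, will be collected". SAEs go to the coordinating centre within 24 hours. The minimum data include the investigator's opinion of the relationship, for which the listed values are "possibly, probably or definitely related".

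Section 10.10 says that "it is impossible to blind treating clinicians and participants". Under Section 14.1 the DSMC or its delegated safety monitor "will review all SAE reports that are received".

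**The concern.** Two sections define a class of reportable event that the third does not collect. A site with an aberration or a study-outcome event that worries the investigator, but that the investigator does not attribute to the allocated strategy, is told by 14.2 or 14.3 that it counts and by 14.4 that it is not gathered. If the site does file it, the listed relationship values oblige it to choose at least possibly related or to leave the item unanswered.

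What is at stake is the AE and SAE stream: which events reach the coordinating centre within 24 hours, which reports the DSMC's safety review sees, and whether sites apply one rule. One site may follow 14.4 literally and file nothing. Another may follow 14.3 and file the event as possibly related. The same event is then recorded differently for reasons unrelated to the patient.

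**Working it through.** No figure in the protocol bears on this point, so the check is a comparison of the three sections and of what is collected elsewhere.

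**Step 1. Cross the criteria.**

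| Event class | Investigator's view | 14.2 / 14.3 | 14.4 |
|---|---|---|---|
| Common aberration | Related, and needing significant intervention | AE | Collected |
| Common aberration | Of concern, judged unrelated | AE | Not collected; no matching relationship value |
| Study outcome (e.g. death, readmission) | Related | SAE | Collected |
| Study outcome | Of concern, judged unrelated | SAE | Not collected; no matching relationship value |
| Either class | Neither related nor of concern | Exempt | Not collected |

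The conflict is confined to the second and fourth rows. The 14.2 sentence can be parsed with the need for significant intervention attached to the first ground only or to both. On either parsing, concern is a ground that requires no causal judgement.

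**Step 2. Is the restrictive reading of 14.4 the natural one?** The commas around the causality clause in "AEs and SAEs, which are deemed causally related to the study intervention by the investigator, will be collected" would allow it to be read as description rather than restriction. The relationship item points the other way: "possibly, probably or definitely related" leaves no value for an unrelated event, as one would expect if only related events were meant to arrive.

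**Step 3. Who makes the judgement?** The site investigator, in an open-label trial. Section 10.1 allows that same investigator to perform the randomisation, so the causal opinion is given with knowledge of the allocation.

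**Step 4. What is captured anyway?** Section 12.2 collects, with no causality test:
- vital status at ICU and hospital discharge, day 28, day 90, and 6 and 12 months;
- cause-specific hospital mortality;
- admission and discharge dates, including readmissions;
- CVC complications, acute pulmonary oedema and ischaemic events.

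The fourth-row examples named in 14.3, death and readmission, therefore stay in the dataset. They miss only the SAE route: the 24-hour report and DSMC review as SAEs.

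**Step 5. What can actually be lost?** Events outside the Step 4 list, chiefly the aberrations of concern in the second row. Even there the loss is partial, because Section 12.2 collects available physiological and laboratory variables during the intervention, up to 24 hours.

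**Step 6. Does anything else move?** The primary outcome (days alive and out of hospital to day 90) and the sample size in Section 13.1 use no AE or SAE data, so neither changes.

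**The case against.** The strongest reply is that this is loose drafting around a sound design. Both arms lie within usual care (Section 11.3), the main anticipated harms are recorded for everyone, and Section 14.2 says that complication outcomes are kept out of AE reporting so that their reporting is unbiased. Restricting the remaining AE and SAE collection to related events is a legitimate choice. The 24-hour sentence in 14.4 carries no causality qualifier, the relationship values appear under minimum data, the web form is not shown, and 'possibly' is a low bar. Section 14.4 also sends significant safety issues to the ethics committee, Section 12.3 provides source data verification, and Section 14.1 lets the DSMC ask for any other trial data.

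Much of this stands and limits the point. It does not remove the contradiction: if the design is to collect related events only, the concern grounds in 14.2 and 14.3 have no function. The DSMC's discretion helps only with data that exist, and the ethics committee route does not lead to the coordinating centre or the DSMC.

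A reader might infer three stronger things that the documents do not support:

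- *That 14.3 tells sites to report any unexpected serious event of concern, and 14.4 then discards it.* The concern ground in 14.3 attaches to events already defined as study outcomes, and that in 14.2 to common aberrations. Neither is a general rule.
- *That attribution by unblinded staff will produce a spurious difference between arms.* This is possible in principle, but the protocol gives no event rate or attribution rate from which to size it, and nothing on which arm would be favoured. Any figure would be invented.
- *That no independent party could look behind a judgement of unrelated.* The DSMC's power to request other data and the monitors' source checks make that too absolute, although neither is an explicit power to re-attribute an unreported event.

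**Conclusion.** The contradiction is real and should be corrected. Under 14.4 as written, an event of concern judged unrelated qualifies as an AE or SAE under 14.2 or 14.3 but has neither a collection route nor a truthful relationship value. It may miss 24-hour reporting and DSMC review of SAEs, and sites may differ in what they file.

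The consequence is modest. It concerns two classes of event. For outcome events and listed complications, what is at risk is expedited reporting and SAE review rather than the data. Actual data loss is confined to other events, and their number cannot be estimated from the protocol. The conclusion assumes that the causality clause in 14.4 restricts collection and that the web form offers only the listed relationship values. If the form has more options, the text still needs reconciling but the practical effect shrinks.

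**What to change.** Amend the first sentence of 14.4 so that it collects, over the same period, AEs and SAEs that are possibly, probably or definitely related, or that are of concern in the investigator's judgement whatever the attribution. Keep the exemptions in 14.2 and 14.3 as they are. Add 'unlikely' and 'not related' to the relationship item in 14.4 and on the web form.

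The cost is one sentence, two response options and a modest number of extra forms, since events that are neither related nor of concern stay exempt. No clinical management changes.

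This brings the three sections into line. It does not make AE and SAE counts free of opinion, because being of concern is also a judgement by an unblinded investigator. How SAEs are tabulated by attribution, and whether the DSMC records its own attribution, can be left to the SAP and the DSMC charter.
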